# Safety and clinical efficacy of the secretome of stressed peripheral blood mononuclear cells in patients with diabetic foot ulcer—study protocol of the randomized, placebo-controlled, double-blind, multicenter, international phase II clinical trial MARSYAS II

**DOI:** 10.1186/s13063-020-04948-1

**Published:** 2021-01-06

**Keywords:** Diabetic foot ulcer, Secretome-based therapy, Peripheral blood mononuclear cells, Skin, Inflammation, (Impaired) wound healing, Biological, Hydrogel, Clinical trial protocol, Randomized controlled trial

## Abstract

**Background:**

Diabetes and its sequelae such as diabetic foot ulcer are rising health hazards not only in western countries but all over the world. Effective, yet safe treatments are desperately sought for by physicians, healthcare providers, and of course patients.

**Methods/design:**

APOSEC, a novel, innovative drug, is tested in the phase I/II study MARSYAS II, where its efficacy to promote healing of diabetic foot ulcers will be determined. To this end, the cell-free secretome of peripheral blood mononuclear cells (APOSEC) blended with a hydrogel will be applied topically three times weekly for 4 weeks. APOSEC is predominantly effective in hypoxia-induced tissue damages by modulating the immune system and enhancing angiogenesis, whereby its anti-microbial ability and neuro-regenerative capacity will exert further positive effects. In total, 132 patients will be enrolled in the multicenter, randomized, double-blind, placebo-controlled, parallel group, dose-ranging phase I/II study and treated with APOSEC at three dose levels or placebo for 4 weeks, followed by an 8-week follow-up period to evaluate safety and efficacy of the drug. Wound area reduction after 4 weeks of treatment will serve as the primary endpoint.

**Conclusion:**

We consider our study protocol to be suitable to test topically administered APOSEC in patients suffering from diabetic foot ulcers in a clinical phase I/II trial.

**Trial registration:**

EudraCT 2018-001653-27. Registered on 30 July 2019. ClinicalTrials.gov NCT04277598. Registered on 20 February 2020. Title: “A randomized, placebo-controlled, double-blind study to evaluate safety and dose-dependent clinical efficacy of APO-2 at three different doses in patients with diabetic foot ulcer (MARSYAS II)”

**Supplementary Information:**

The online version contains supplementary material available at 10.1186/s13063-020-04948-1.

## Background

According to the World Health Organization (WHO), diabetes is on the rise: the number of persons suffering from diabetes increased from 108 million in 1980 to 422 million in 2014. The global prevalence of diabetes among adults over 18 years of age has risen from 4.7% in 1980 to 8.5% in 2014 [1]. Major complications of diabetes mellitus are the development of foot ulcers and impaired wound healing. The International Working Group on the Diabetic Foot defines a foot ulcer as a full-thickness wound involving the foot or ankle [2]. Non-healing, chronic wounds predominantly remain in early inflammatory stages of wound healing, lacking the controlled synchronization and succession of events that lead to rapid and complete healing. With regard to diabetic ulcers, healing impairment is caused by several intrinsic factors (neuropathy, vascular problems) and extrinsic factors (wound infection, callus formation, and excessive pressure to the site). By definition, this set of predisposing abnormalities in diabetes has been referred to as the “pathogenic triad” of neuropathy, ischemia, and trauma. One abnormality in the wound healing process can lead to another, generating a pathogenic vicious circle in diabetes [3]. Despite better understanding of the underlying disease pathology and improved care of diabetic foot ulcers (DFUs), foot complications are still the most frequent reasons for hospitalization of diabetic patients [4]. Delayed healing of DFU and further related problems (e.g., neuropathy and unnoticed injuries, tissue necrosis, sepsis) are the primary factors leading to lower extremity amputation and death. Moreover, about 50% of patients undergoing foot amputation develop an ulcer in the contralateral limb within 18 months of surgical intervention [5]. Nearly half of all unhealed neuropathic ulcers lead to death within 5 years [6]. In spite of the severe consequences of DFU, no effective medicinal product for treating non-healing ulcers is currently available.

Standard of care: The clinical practice guidelines of the Austrian and German Diabetes Association [7, 8] are in accordance with the British NICE guideline for diabetic foot problems for DFU prevention and management (published: 26 August 2015 nice.org.uk/guidance/ng19) by recommending a multidisciplinary management of diabetic foot complications including measures such as metabolic optimization and treatment of underlying medical diseases, infection control, debridement of devitalized tissue, effective relief from pressure, local wound treatment, therapy of vascular diseases, and education of patients. Adjuvant therapies (e.g., hyperbaric oxygen therapy, cell therapy) are considered to be reserved for patients classified as Wagner stage > 3 in cases, when all treatment possibilities of revascularization have been exhausted and the threat of lower limb amputation is looming. The NICE guideline does not recommend advanced treatment (e.g., using stem cells or tissue transplantation) outside of a clinical trial setting.

MARSYAS II is the first clinical trial to test a secretome-based therapy in DFU. The origins of the tested drug APOSEC go back to stem cell therapy which was investigated in a field of regenerative medicine. This name resumes the expectations of the investigators of the time at the turn of the millennium to be able to regenerate harmed body tissue by applying cells to it that differentiate themselves into new tissue cells. Stem cells were widely used to treat tissue damages with focus on heart failure [9, 10]. However, promising preclinical results often fell far short of expectations in large controlled clinical trials [11]. Meanwhile, the secretome of stem cells showed promising results in tissue repair (including heart, nerves, or skin) indicating that released factors induce regeneration rather than the cells themselves [12–15]. This approach was known as the “paracrine hypothesis” in stem cell research.

The development of APOSEC started with the use of stressed peripheral blood mononuclear cells (PBMCs) instead of stem cells. Based on the findings of Holzinger and colleagues (they used autologous mononuclear cells to treat patients with non-healing skin ulcer [16]), [name] and his research group demonstrated that irradiated mononuclear cells and their secretome exhibit similar therapeutic effects compared to those of stem cells. At first, the PBMCs were used together with their secretome until it was found out that the therapeutic effect is exerted by the secretome alone. In several studies, it could be shown that the secretome is rich in factors preventing tissue damage and promoting tissue repair in heart failure [17, 18]. The advantage of PBMCs compared to stem cells is that they can be isolated more easily and in larger amounts and that they are a waste product of blood transfusion units. Moreover, the use of the secretome without cells but with all favorable factors has decisive virtues over cell-containing products, e.g., in the possibility of viral clearance [19], better storage options, longer shelf life, and easier handling in the application to the patient.

The secretome released by stressed PBMC is an innovative and new biological drug. The drug substance called APOSEC contains a large variety of biomolecule classes, including proteins, extracellular vesicles, anti-microbial peptides, nucleotides, and lipids. It is produced according to good manufacturing practice using buffy coats of strictly selected healthy blood donors and undergoes two orthogonal virus reduction steps to provide a safe high-quality product [19]. The drug product for the investigational medicinal product (IMP) of MARSYAS II is called APO-2, which is APOSEC mixed with hydrogel for topical application.

Preclinical studies showed in experimental small and large animal models that the intravenous application of APOSEC (APO-1, APOSEC in saline solution) attenuates acute and latent myocardial infarction [20, 21], stroke [22], and spinal cord injury [23] and that topical application of APOSEC (APO-2) improves wound healing [24, 25]. Mode of action (MOA) investigations revealed that APOSEC is effective in treating hypoxia-induced tissue damages by employing a large number of different MOAs. APOSEC exerts cytoprotective and regenerative effects. On the one hand, APOSEC prevents the organism from effects of overreaction by the immune system; on the other side, it stimulates certain aspects of tissue regeneration and wound healing. For example, APOSEC induces effects that prevent tissue destruction like platelet inhibition and vasodilation [26] and increased expression of cytoprotective and anti-apoptotic genes in primary cultured human cells [18, 27]. On the other hand, APOSEC also induces effects that promote tissue regeneration and wound healing like enhanced migration of fibroblasts and keratinocytes [27] and increased sprouting of aortic and spinal cord endothelial cells in vitro [23, 25]. Furthermore, it exerts antibacterial activity [28]. No single effective component could be determined in MOA studies [18, 23, 28]. On the contrary, it was shown that the biological activity of individual fractions of APOSEC tested in selected potency and cell-based assays in vitro is significantly inferior compared to that of the entire secretome [25, 29]. This suggests that the effect of APOSEC depends on the synergy of its components. Hence, in the MARSYAS II trial, the multi-faceted disease of DFU will be met by a pleiotropic drug exerting various effects.

## Methods/design

### Study setting

The clinical study protocol (CSP) of the MARSYAS II trial was written in accordance with the Recommendations for Interventional Trials (SPIRIT) guidelines and completing the SPIRIT Checklist (see supplemental file). The study was approved by the Austrian health authorities (Austrian Office for Safety in Health) and the local Austrian ethics committees (Linz and Klagenfurt). A thorough feasibility and site qualification was performed prior to the selection of 16 study sites in 4 countries (Austria, Germany, Poland, and the Czech Republic) to ensure the achievement of adequate participant enrollment to reach the calculated target sample size. The clinical research organization (CRO) FGK Clinical Research GmbH (Munich, Germany) and its subsidiaries in the Czech Republic and Poland will coordinate the centers and are responsible for data management and pharmacovigilance. Any protocol modifications will be timely reported to the respective authority.

The primary objective of the MARSYAS II trial is to determine the dose-response relationship of the clinical efficacy of APO-2 multiple dose administration in patients with diabetic foot ulcer at three different dose levels compared to placebo. The secondary objectives are to evaluate the safety and tolerability of APO-2 at three different doses and to generate data on additional clinical endpoints for the conception of a phase III study.

The study design is shown in Fig. 1. The partners of the safety lead-in phase are listed in Table 1.

**Fig. 1 Fig1:**
[figure not shown]
Study design of the MARSYAS II study

**Table 1 Tab1:** Partners in the safety lead-in phase of the MARSYAS II study

Sponsor	Aposcience AG
CRO	FGK Clinical Research GmbH
Service provider for IMP storage and distribution	ABF Pharmaceutical Services GmbH
Drug manufacturer	Austrian Red Cross, Blood Transfusion Service for Upper Austria
Safety lead-in	
Study center 1	Kepler Universitaetsklinikum Linz
Study center 2	A.oe. Krankenhaus der Elisabethinen Klagenfurt
Backup study center 1	Fakultní nemocnice u sv. Anny, Brno
Backup study center 2	Fakultní nemocnice Královské Vinohrady, Prague
Backup study center 3	Ústřední vojenská nemocnice - Vojenská fakultní nemocnice, Prague

The study design is based on the results and experiences of the clinical study MARSYAS I, where the topical application of autologous APOSEC was tested in healthy volunteers. The study MARSYAS II is divided into a main study phase (phase IIa, parallel group, four-arm, exploratory trial with equal allocation ratio and superiority testing for secondary endpoints) and a safety lead-in phase (phase I, parallel group, two-arm, exploratory trial with 3:1 allocation ratio) which precedes the main phase and evaluates the safety of the IMP. In the safety lead-in phase, only the medium dose is administered. Between screening and randomization visit, a run-in time period of a minimum of 2 weeks is implemented to observe if the wounds heal when treated with standard of care (SoC) and to include only patients with impaired wound healing.

After the run-in period, the treatment period starts and lasts for 4 weeks, followed by an 8-week follow-up period without application of IMP but with continuation of treatment with SoC.

### Standard study procedures

Before inclusion of a patient into the study, written informed consent will be obtained after disclosure of all aspects of the trial by a physician. The investigator will verify that all inclusion, exclusion, and randomization criteria are met, and all other requirements of the study protocol are fulfilled. The eligibility criteria are listed in Table 2. Patients will be enrolled in various clinical settings, including outpatients from specialized wound management clinics and inpatients from tertiary care setting. The visit schedule is shown in Table 3. On the informed consent form, participants will be asked if they agree to the use of their data: medical findings and personal information will be collected and written down in their personal file at the site; a transfer of the data, in particular to the sponsor, takes place only in pseudonymized and encrypted form. This trial does not involve collecting biological specimens for storage. During their participation in the clinical study, patients will be insured as defined by legal requirements.

**Table 2 Tab2:** Inclusion/exclusion criteria

Inclusion criteria	
○ Patient is between 18 and 80 years of age	
○ Patients with type I or type II diabetes with a glycosylated hemoglobin (HbA1c) of ≤ 12%, obtained at enrollment or within 30 days prior to study enrollment	
○ Patients who have a wound defined as diabetic foot ulcer present for ≥ 4 weeks	
○ Foot ulcer Wagner grade I–II or ARMSTRONG grade I-A (superficial, non-infected, non-ischemic wound not involving the tendon, capsules, or bone) or II-A (non-infected, non-ischemic wound penetrating to tendon or capsule but not to the bone or joint)	
○ Estimated foot ulcer surface area between ≥ 1 and ≤ 8 cm^2^ as measured at the day of randomization assessed using the eKARE imaging and measurement device	
○ A patient with more than one diabetic foot ulcer may be included in the study but only one ulcer will be selected for the investigational treatment based on investigator judgment as far as the ulcer meets the inclusion criteria (the largest ulcer fitting the inclusion criteria will be selected as index ulcer)	
○ Wound area has not changed by more than 30% between screening visit and randomization visit (at least 14 days)	
○ Adequate arterial blood perfusion (ABI [ankle brachial index] between 0.7 and 1.3 [the highest ABI measured value will be used as a reference], or toe pressure > 50 mmHg, or tcPO2 > 40 mmHg) within the past 6 months	
○ Patient must adhere to off-loading of the ulcer area (in mobile patients, adherence to off-loading footwear during the study is mandatory)	
○ Patient is able to give written informed consent prior to study start and to comply with the study requirements	
○ Women of childbearing potential agree using adequate birth control methods during the study	
Exclusion criteria	
○ History of anaphylaxis, known hypersensitivity to sodium alginate, propylene glycol, methylene blue, or chicken egg	
○ Target ulcer is over a deformity (such as Charcot deformity) that interferes with off-loading based on investigator’s opinion	
○ Index wound duration of > 52 weeks without intermittent healing	
○ Clinical evidence of ulcer bed infection or patients requiring intravenous (IV) antibiotics to treat the index wound infection at time of randomization	
○ Current evidence of osteomyelitis, cellulitis, or other evidence of infection including pus drainage from the wound site, or documented history of osteomyelitis at the target wound location during the 6 months preceding the screening visit	
○ Major uncontrolled medical disorder(s) such as severe uncontrolled leg edema, concurrent medication, or other issues that render the patient unsuitable for participation in the study, including but not limited to comorbid condition with an estimated life expectancy of ≤ 12 months, hemoglobin A1c (Hba1c) > 12% at screening, patients on dialysis, patients with severe pulmonary (requiring home oxygen, uncontrolled COPD Gold III/ IV) or cardiovascular conditions (heart failure NYHA IV, uncontrolled hypertension systolic BP by repeated measurement > 180 mmHg)	
○ Raynaud disease or any other severe peripheral microvascular disease, current diagnosis of vasculitis, or current diagnosis of claudication	
○ Dermatologic comorbid disease, history of systemic lupus erythematosus with elevated anti-DNA antibody titers, Buerger’s disease (thromboangiitis obliterans)	
○ Patient currently treated for an active malignant disease or prior diagnosis of an active malignant disease who is disease free for less than 1 year. Treatment with anticancer therapy (chemotherapy, immunotherapy, radiotherapy, targeted therapy, or gene therapy) within 3 months before the first administration of the investigational product or at any time during the study	
○ Patient with a history of malignancy within the wound; history of radiation therapy to the wound region	
○ Patients who have undergone wound treatments with growth factors, dermal substitutes, or other biological therapies within the last 30 days or during the study	
○ Patients who received oral or parenteral corticosteroids, immunosuppressants, or cytotoxic agents within 30 days preceding the first study drug administration, or plan to use these medications during the study period	
○ Patients who are pregnant or breastfeeding	
○ Mental condition rendering the patient (or the patient’s legally acceptable representative[s]) unable to understand the nature, scope, and possible consequences of the study	
○ Patients who are incarcerated, including prisoners or patients compulsorily detained for treatment of either a psychiatric or physical (e.g., infectious disease) illness	
○ Therapy with another investigational agent within 30 days of screening, or during the study	
○ Patients who are considered by the investigator to have a significant disease, which can impact the study; patients who are considered not suitable for the study by the investigator	
○ Employee at the study site, spouse/partner or relative of any study staff (e.g., investigator, sub-investigators, or study nurse), or relationship to the sponsor	
Prohibited medication	
○ Oral or parenteral corticosteroids of > 20 mg/week within the past 4 weeks before the screening and during the course of the study (intranasal or inhaled steroids for allergies/asthma or COPD are allowed)	
○ Immunosuppressive or cytotoxic agents within 30 days preceding the first study drug administration and during the study period	
○ Wound treatments with growth factors, dermal substitutes, or other topical biological therapies within the last 30 days of screening and during the study duration

**Table 3 Tab3:** Visit and treatment schedule

Periods	Enrollment/screening	Allocation	Active treatment	Follow-up/close-out			
Visits	Visit 1	Visit 2	Visit 3 to visit 13	14 (EOT)	15	16	17
Days from randomization visit	Days -14 to -28 (prior to active treatment)	Day 0	Day 1 to day 28	Day 30 (± 5 days)	Day 44 (± 2 days)	Day 56 (± 2 days)	Day 84 (± 5 days)
**Enrollment**							
**Informed consent**	X						
**Inclusion/exclusion criteria**	X	X					
**Demography**	X						
**Medical history**	X						
**Concomitant medication**	X	X	X	X	X	X	X
**Interventions**							
**Randomization**		X					
**IMP application (verum)**		X	X				
**IMP application (placebo)**		X	X				
**Assessments**							
**Physical examination and vital signs**	X	X		X			X
**Hematology**^a^	X						X
**Serum chemistry**^b^	X						X
**Urine analysis**^c^	X						X
**Urine pregnancy test**	X	X		X			
**Wound assessment**	X	X	X	X	X	X	X
**Assessment of wound closure**	X	X	X	X	X	X	X
**Wound size measurement (eKare inSight®)**	X	X	X	X	X	X	X
**Standard of care for wound management**	X	X	X	X	X	X	X
**VAS—score for pain**	X	X	X	X	X	X	X
**Neurological assessment foot**		X		X			X
**Chronic wound quality of life questionnaire**		X		X			X
**Recording adverse events**		X	X	X	X	X	X

^a^Erythrocytes/leucocytes/hemoglobin, hematocrit, thrombocytes, MCV, MCH, and MCHC

^b^Sodium, potassium, total protein, albumin, BUN, creatinine, glucose, Hba1c, AST, ALT, GGT, total bilirubin, and CRP

^c^Urine dip stick: pH, nitrite, glucose, leucocyte, ketone, bilirubin, protein, and blood

In the safety lead-in period, a minimum of 12 patients will be enrolled and randomly assigned (3 active: 1 placebo) to receive the medium dose of APO-2, (25 U/ml, 9 patients) or placebo (3 patients). Randomization is done by computer-generated random numbers, and the information is only given to the pharmacist who prepares the IMP. Safety assessments of patients in the safety lead-in period will include recording of adverse events (AEs), use of concomitant medications, and wound size measurement. Immediately after the last randomized patient reaches the end of treatment with IMP, safety and efficacy data of the safety lead-in period will be reviewed by an independent Data and Safety Monitoring Board (DSMB). During this evaluation, study enrollment will be paused and only the active patients will be followed up. The DSMB board consists of three independent experts in the field of clinical wound care and one statistician.

After a review of the safety results, the DSMB will make a recommendation as to whether or not the main study may start as designed (i.e., randomized, double-blind, parallel group). The DSMB may also recommend the inclusion of additional patients in the safety lead-in period prior to initiation of the main study. After the DSMB decision, the patients in the safety lead-in period will continue to be followed as per protocol completing the 8-week follow-up period after the last administration of the investigational product. Besides the DSMB, no other interim analyses or formal stopping rules are intended.

For the main study, eligible patients will be stratified by wound size (at least one third of patients are required to have wound size > 4 cm^2^) and randomly assigned to 1 of 4 treatment groups (low dose, medium dose, high dose, or placebo).

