### Statistical analysis

For the preceding safety lead-in part of the study, safety data of 12 randomized patients will be summarized after the 4-week treatment period. These data will be evaluated by the DSMB. Unblinding is not planned but is possible if requested by the DSMB. Safety and efficacy results of the safety lead-in phase will be included in the data pool of the entire clinical study for final analysis (i.e., the safety lead-in phase is an integral part of the entire MARSYAS II study).

The main study is designed to evaluate the dose-response relationship for clinical efficacy of topical APO-2 at three dose levels compared to placebo. The minimum effective dose, which is defined as the smallest dose with a discernible, useful effect, will be determined.

The primary endpoint is the assessment of the dose-related, relative reduction in wound area from baseline to week 4 (continuous endpoint). Analysis of the primary and secondary efficacy variables will be based on the full analysis set (i.e., all patients with a measured wound size at baseline, who received at least one dose of IMP and have data available at the end of treatment visit). Details are defined in a statistical analysis plan. If data are normally distributed, one-way analysis of variance (ANOVA) will be calculated, including a Dunnett multiple comparison post hoc test, to test each of the active doses against placebo. If Gaussian distribution is not given, a non-parametric Kruskal-Wallis test with Dunns post hoc tests will be performed. If at least one of the doses is statistically significant, then the dose-response relationship is established. In addition, a dose-response model will be developed and tested. Three candidate models (linear, quadratic, and logistic) will be fitted to the data and the Akaike Information Criterion will be used to select the best model. Confidence bands for the estimated dose-response curve will be presented. Binary endpoints will be analyzed by displaying the number and percentage of patients in each dose group. Differences among dose groups will be tested using Fisher’s exact test. For the evaluation of the continuous endpoints, data will be analyzed as absolute values and changes from baseline will be represented by basic statistics (mean, standard deviation, minimum, first quartile, median, third quartile, maximum). A detailed description of the reports and tests is specified in a statistical analysis plan.

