On the basis of experiences in preclinical wound models and the MARSYAS I clinical trial, we believe that the selected doses of 12.5 U/ml, 25 U/ml, and 50 U/ml are safe for topical administration in DFU patients. All three doses have been used in preclinical proof-of-concept studies of wound models where APO-2 promoted wound healing (closure) [24, 25]. Both the low and the medium dose have been used in the clinical phase I trial MARSYAS I daily for 7 days [31]. The selected doses are within a reasonable safety margin relative to the doses used in non-clinical toxicology studies (10 times lower than the highest dose used in toxicological studies, Table 4) [36].

The rationale for the treatment frequency and duration is based on own non-clinical studies and previously published data by Holzinger et al. using similar drug compounds in patients with chronic wound ulcers [16]. Regular assessment of wound size and characteristics during the phase II trial will allow for further dose adaptation in the pivotal phase III trials. We know from pre-study visits and questionnaires answered by the chosen principal investigators that predominantly small wounds occur. Therefore, a stratification is implemented in the main study that a minimum of one third of patients are required to have wound size > 4 cm^2^.

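### Main-study randomisation is stratified by wound size, but none of the named tests includes the stratum or baseline area, so precision is lost if wound size predicts relative area reduction

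*Protocol article*

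**What the plan says.** **Randomisation.** Under Standard study procedures (text after Table 3), the rule for main-study allocation reads: "eligible patients will be stratified by wound size (at least one third of patients are required to have wound size > 4 cm^2"; patients are then allocated at random to low, medium or high dose or placebo. The Discussion gives the reason: sites expect mostly small wounds, so "a minimum of one third of patients are required to have wound size > 4 cm^2". Table 2 limits the baseline wound: "Estimated foot ulcer surface area between ≥ 1 and ≤ 8 cm^2^ as measured at the day of randomization".

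**Endpoint.** The Statistical analysis section defines the primary endpoint as the "dose-related, relative reduction in wound area from baseline to week 4".

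**Tests.** The same section names the analyses. If the data look normal, "one-way analysis of variance (ANOVA) will be calculated, including a Dunnett multiple comparison post hoc test"; otherwise "a non-parametric Kruskal-Wallis test with Dunns post hoc tests will be performed". For binary endpoints, "Differences among dose groups will be tested using Fisher’s exact test". No stratum term, baseline covariate or stratified version of any test is named. Details are deferred to a statistical analysis plan that is not shown. The 12 planned lead-in patients (9 medium dose, 3 placebo) are pooled into the final analysis, and no stratification is described for them.

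**The concern.** A one-way ANOVA has dose as its only factor. Kruskal-Wallis and Fisher's test, as named, carry no stratum. The article therefore does more than leave covariates open: it fixes tests that exclude the factor on which allocation was balanced.

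Stratified allocation makes the arms alike in wound size, so the true variance of the difference between arm means contains only the within-stratum part. An unadjusted analysis estimates its error from the whole within-arm variance, including the difference between strata. If wound size is prognostic, that estimate is too large, the standard errors of the dose-placebo differences are too large, and power is lost.

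The trial is meant to find a minimum effective dose from dose-placebo comparisons, so precision matters most for the smaller differences.

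**Working it through.** **Inputs from the protocol article** (Sample size calculation and power): expected reductions 0.40, 0.45, 0.50, 0.55; variance of means V = 0.003; within-group SD = 0.156; two-sided alpha 0.05; power 80%; 23 per group. **Assumption, not in the document:** the correlation rho (multiple correlation if both covariates are used) between baseline wound size and relative reduction within arms, taken from 0 to 0.5.

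**1. The plan's own figure.** The mean of the four reductions is 0.475. The squared deviations sum to 2 × 0.075² + 2 × 0.025² = 0.0125, so V = 0.0125/4 = 0.003125, printed as 0.003. For the four-group F test, lambda = 4nV/SD² with 3 and 4(n − 1) df, and SD² = 0.024336.

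- V = 0.003125, n = 23: lambda = 92 × 0.003125/0.024336 = 11.81, power 81.5%. At n = 22, power is 79.5%. The stated 23 is reproduced.
- V = 0.003 as printed, n = 23: lambda = 92 × 0.003/0.024336 = 11.34, power 79.8%; 24 would be needed. The gap is rounding.

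The sample size thus rests on the unadjusted one-way ANOVA and is right for that test.

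**2. Power with adjustment.** Residual SD = 0.156 × √(1 − rho²), so lambda becomes 11.34/(1 − rho²). Two error df are charged (stratum and log baseline area), leaving 88 − 2 = 86. With V = 0.003 and n = 23:

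| rho | variance explained | residual SD | lambda | power |
|---|---|---|---|---|
| no covariates | – | 0.1560 | 11.34 | 79.8% |
| 0 | 0% | 0.1560 | 11.34 | 79.7% |
| 0.1 | 1% | 0.1552 | 11.46 | 80.2% |
| 0.2 | 4% | 0.1528 | 11.81 | 81.5% |
| 0.3 | 9% | 0.1488 | 12.46 | 83.7% |
| 0.5 | 25% | 0.1351 | 15.12 | 90.6% |

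At rho = 0 the covariates cost about 0.1 point.

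**3. Behaviour of the unadjusted test after stratified allocation.** Simulation: 24 per arm, one third in the larger-wound stratum in every arm, total within-arm SD 0.156, 20,000 runs. If the strata differ by d in mean reduction, the stratum explains R² = (1/3)(2/3)d²/0.024336.

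| d | R² | type I error, unadjusted | type I error, adjusted | power, unadjusted | power, adjusted |
|---|---|---|---|---|---|
| 0.05 | 0.02 | 4.7% | about 5% | 83.3% | 84.1% |
| 0.10 | 0.09 | 3.5% | about 5% | 83.7% | 87.3% |
| 0.15 | 0.20 | 1.9% | about 5% | 84.1% | 91.6% |

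These runs use the unrounded means and 24 per arm, so the power levels sit above those in step 2. The direction is the point: the unadjusted test never exceeds 5%.

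**4. Dose-placebo comparisons.** Under the plan's means, Dunnett power for the medium dose (0.50 against 0.40) is about 42% at 23 per group without covariates. With two error df charged, it is about 46% at rho = 0.3 and 55% at rho = 0.5.

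**The case against.** **Purpose.** The Discussion presents the one-third rule as a way to secure enough larger wounds. It works at least partly as an enrolment quota, and the document nowhere calls wound size prognostic. This stands: one cannot say that the authors stratified to gain precision. The text still stratifies patients and then randomises them, so the mismatch with the tests remains.

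**Size.** No correlation is given, and an endpoint already expressed relative to baseline may depend little on wound size. This stands, and is why the range starts at zero.

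**Power is not in danger.** The target is 80%, and 132 patients are planned. If 12 are lead-in patients, (132 − 12)/4 = 30 per group remain, a figure the document does not itself state. The unadjusted F test then has 90.3% with V = 0.003. The main study is also labelled exploratory. A reader might infer that the trial is underpowered or its test invalid; the documents support neither.

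**Deferral to the analysis plan.** Covariates often go there. But the article names the tests, and adding a stratum would replace a one-way ANOVA, not fill in its detail.

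**Two tempting extensions that fail.** A reader might infer that, because baseline area is the denominator, any chance imbalance in it passes directly into the endpoint. It does not: relative reduction is scale-free, and an arm's mean shifts only if relative reduction itself depends on wound size. A reader might also infer that intervals for binary endpoints are too wide. For these the article specifies counts, percentages and Fisher's p-value, so the interval argument is confined to the primary endpoint.

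**Conclusion.** The point holds as a matter of efficiency. The article stratifies main-study randomisation by wound size and names tests that use neither the stratum nor baseline area. If wound size predicts relative reduction, the unadjusted primary test is conservative and imprecise; it is not biased and does not inflate type I error.

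The gain from adjusting at 23 per group runs from nothing (rho near 0) to about 11 points of F-test power (79.8% to 90.6% at rho = 0.5). It rests wholly on an assumed correlation and on the plan's own means and SD. The stated 23 per group is not wrong for the test named.

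Pooling the lead-in patients is a further reason to adjust. They enter only the medium-dose and placebo arms, at 3:1, with no stratification described, so balance on wound size is not assured in the pooled data.

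**What to change.** - **Primary analysis:** ANCOVA of relative reduction on dose group, wound-size stratum and log baseline area, with Dunnett-adjusted dose-placebo contrasts from that model.
- **Non-parametric fallback:** a stratified rank test, for example van Elteren, in place of Kruskal-Wallis with Dunn, with multiplicity adjustment over the three dose-placebo comparisons.
- **Binary endpoints:** a CMH or stratified exact test by wound-size stratum, in place of the unstratified Fisher's test.
- **Lead-in patients:** assign them to a stratum from the wound area measured at the randomisation visit.
- **Sensitivity analyses:** keep the unadjusted tests now named.

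The cost is one or two error degrees of freedom and a change of wording in the protocol and analysis plan, made before unblinding. Table 3 already schedules wound size measurement at the randomisation visit, so no new data are needed, and the sample size can stay as it is.
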